## Abstract

**Background:**

Dementia is a neurodegenerative syndrome characterized by impaired cognitive functions associated with psychological and behavioral disorders. The informal caregiver has a central role in the life of the person with dementia. Committing a large part of the day to caring for the assisted person inevitably has an effect on the caregiver’s life.

**Objective:**

The aim of this study is to analyze the impact of a psychosocial intervention dedicated to a group of informal caregivers of patients with Alzheimer disease. The intervention will be guided by a trained psychologist who will facilitate the participants’ expression of their emotional states, as compared to a traditional self-help group.

**Methods:**

The intervention described in this paper was designed and developed for the project INNovazione sociale e tecnologica per le FAMIGLIE che assistono malati affetti da Alzheimer (InnFamiglia). The study is designed as a randomized controlled trial (RCT). The RCT includes an experimental group, in which the participants will undertake the psychosocial intervention, and a control group, where participants will receive support according to traditional self-help methodology. Interventions for both groups will last 4 months and will be comprised of 16 sessions.

**Results:**

Participant recruitment, enrollment, and data collection began in 2021. Enrollment continued until September 2022, at which time the last group began the intervention. Data collection will be completed by December 2022, and data analysis will be completed by March 2023. The study findings will be published in peer-reviewed scientific journals and will be presented at scientific meetings. Summaries of the results will also be made available to investigators for dissemination within their clinics.

**Conclusions:**

We hypothesize that the experimental group will be more effective in managing caregiver burden and coping strategies and that this will improve the perception of well-being, anxiety, and depression among caregivers. Our study aims to compare two groups receiving different interventions: a self-help group and a psychosocial group with elements of emotional support. This study may also give us more information about the most appropriate ways to support and help caregivers of people with dementia.

**International Registered Report Identifier (IRRID):**

DERR1-10.2196/37496

## Introduction

Dementia is a neurodegenerative syndrome characterized by impaired cognitive functions associated with psychological and behavioral disorders. Dementia causes a significant reduction in the autonomy of daily life, making it one of the main causes of a lack of self-sufficiency among the older adult population. It is not a specific disease but rather a “family of diseases,” of which Alzheimer disease is the best known and the most prevalent [1].

According to the Dementia Observatory of the Istituto Superiore della Sanità in Italy, the total number of people with dementia is estimated at over 1 million; about 60% of these people have Alzheimer disease. In addition, an estimated 3 million people are directly or indirectly involved in the informal care of people with dementia [2].

Among the European countries, Italy has one of the highest incidences of dementia among its population. In particular, according to the estimates provided by the United Nation’s World Population Prospects from 2018, Italy is second in terms of the number of people with dementia (n=1,279,366); Germany is first, with about 1.5 million people with dementia (n=1,585,166). France follows with an estimated number of people with dementia similar to that of Italy (n=1,227,558). There were estimated to be over 55 million people worldwide living with dementia in 2020. This number will almost double every 20 years, reaching 78 million in 2030 and 139 million in 2050. Much of the increase will be in developing countries. Currently, 60% of people with dementia live in low- and middle-income countries, but by 2050 this number will increase to 71%. The fastest growing older populations live in China and India and in their South Asian and Western Pacific neighboring countries. According to a projection based on these data, in 2050, 4.13% of Italy’s population will be suffering from dementia. This significant increase seems to be correlated with the average rate of aging among the Italian population, with the population older than 85 years doubling [3-5].

Informal caregivers have a central role in the lives of people with dementia because they represent both the person responsible for care and the figure who consistently provides emotional support, day after day.

In most cases, the children of people with dementia play the role of caregiver, particularly daughters; 64.2% of caregivers are the patients’ children. However, the percentage of partners as caregivers is growing—from 25.2% in 2006 to 37% in 2015—especially if the patient is male. This finding also explains the increase in the proportion of sick people living in their own homes, especially if they live alone with their partner [6].

The caregiver devotes an average of 4.4 hours of direct care and 10.8 hours of supervision to the patient with Alzheimer disease each day. Committing a large part of the day to caring for the assisted person inevitably affects the caregiver’s work life. About 59.1% of currently employed caregivers report changes in work life, and the most-cited consequence is repeated absences (37.2%), especially among men (62.5%). Women, compared to men, indicate more frequently that they have requested part-time work schedules (26.9%). In addition, 29.5% of caregivers take time off from work [6]. Among currently unemployed caregivers, 18.7% reported changes in work life that in some cases coincided with the most extreme consequence: job loss [6].

The caregiver’s commitment also has consequences on their state of health, especially among women, and shows up as fatigue, reported by 80.3% of women as compared to 68.8% of men; lack of sleep (63.2%); symptoms of depression (45.3%); and frequent diseases (26.1%). In addition, a large percentage of caregivers take medications due to the health consequences caused by the immense commitment involved in the care of the patient [6]. There are also negative effects on the caregiver’s relational and social life, from the interruption of activities outside of work (76.0%) to the negative impact on family members (59.7%) and friendships (45.6%) [6].

Caregiver burden is a syndrome that represents the degree to which caregivers negatively perceive their own stress as a result of taking care of their assisted family member. The caregiver can experience problems from a multidimensional perspective, at emotional, social, financial, physical, and spiritual levels [7].

Risk factors for caregiver burden include the following: female sex, low level of education, living with the cared-for person, depression, social isolation, financial strain, high number of hours caring for the sick person, and no other help in caring [8].

Caregivers may suffer from various diseases, such as depression; may have inadequate coping strategies; and may perceive themselves as having a poor quality of life. This may result in physical and psychological symptoms, with which they try to cope by abusing drugs, as compared to noncaregivers [1,9,10]. Support for caregivers is also essential for the well-being of people with dementia. In fact, caregiver characteristics and their perceived burden are factors that are related to the well-being of the person with dementia: high caregiver burden is associated with a higher use of antipsychotic drugs by the patient and a higher risk of institutionalization [11].

Meta-analysis studies revealed that psychosocial interventions had significant effects on caregiver burden, depression, and general health, although the overall effect on quality of life was not statistically significant. The literature also suggests that psychoeducational programs may offer the greatest benefit in relation to reducing the burden of care, while multicomponent and alternative interventions may be better suited to coping with depression [12].

Even cognitive behavioral approaches are promising, especially for the reduction of depressive symptoms, while psychoeducational interventions can instead reduce the subjective load of the caregiver. In particular, the subjective load seems to be the factor that most improves with psychosocial interventions for the caregiver [13]. As seen in the literature, the approaches used to support caregivers focus more on educational support, education, social skills, cognitive behavioral support, information, and psychoeducational support [14].

Among the interventions for caregivers, support groups have been shown to be effective. In this type of group, caregivers meet each other and freely discuss their practical experiences and their emotional experiences, in particular. These groups can help the person experience the difficult task of caregiving more calmly and consciously.

Caregivers may have the opportunity to discuss common problems, to receive useful information from other people living in similar situations, to increase their coping strategies, and to have emotional support regarding the experience of the disease [6,15,16].

Support groups are one of the most important interventions: people face the same problems and share their experiences through mutual help [15,17-19]. These kinds of groups provide the caregiver with a comfortable environment where they can share their emotions, reduce stress and caregiver burden, alleviate social isolation, and improve quality of life. The World Alzheimer Report 2015 reported that there is a need to strengthen services for caregivers of Alzheimer patients in order to reduce their burden by making health workers aware that caregivers are an essential part of ongoing care for the Alzheimer patient [20,21].

Following these reviews in the literature, it seems important to assess the effectiveness of group interventions in supporting the family caregiver of the person with Alzheimer disease.

The intervention described in this paper was designed and developed for the project INNovazione sociale e tecnologica per le FAMIGLIE che assistono malati affetti da Alzheimer (InnFamiglia), funded by Fondazione Cariverona. The project aimed to support older people affected by Alzheimer disease and their families throughout the duration of the disease, from initial subjective memory complaints to the severe dementia phase, overcoming the fragmentation of the services available in the local community. The project, in fact, will exploit an ecosystem of innovative services, designed in a participatory approach with the older patients, their families, and local stakeholders. The services will include the following: the development of physical and cognitive interventions, integrated with technological solutions to slow down and prevent disease progression; the availability of a daily care center for patients at the mild to moderate stages; the delivery of specialized training to a multidisciplinary team for home assistance of patients at the severe stage; and the provision of tailored interventions to support and educate informal caregivers, such as the one discussed in this paper. The study presented in this paper aims to analyze the impact of a psychosocial intervention provided to a group of informal caregivers of patients with Alzheimer disease, guided by a trained psychologist for facilitating the expression of emotional states, compared to a traditional self-help group. The factors observed and evaluated in the assessment will be the caregivers’ depression and coping strategies, caregiver burden, and their perceived quality of life.

## Methods

### Study Design

The study is designed as a randomized controlled trial (RCT). The RCT will include an experimental group, in which participants will undertake the psychosocial intervention, and a control group, where participants will receive support according to the traditional self-help methodology. Interventions for both groups will last 4 months and will be comprised of 16 sessions. The following evaluation phases are planned: T0 (baseline), T1 (end of treatment), and T2 (follow-up at 6 months). At each stage, a self-assessment questionnaire will be administered as described in Multimedia Appendix 1. Figure 1 describes the experimental design.

**Figure 1 figure1:**
[figure not shown]
Experimental design of the randomized controlled trial. INRCA: Istituto Nazionale di Ricovero e Cura per Anziani.

### Participants, Recruitment, and Sample Size

The sample consists of family caregivers of people with Alzheimer disease who are followed by the Alzheimer Center of the Istituto di Ricovero e Cura a Carattere Scientifico (IRCCS) Istituto Nazionale di Ricovero e Cura per Anziani (INRCA) of Ancona. No limits are set for the ages of both the patient and the caregiver, nor for the type of family relationship between them.

Eligibility criteria for caregivers include the following:

Signed an informed consent formAged 18 years or olderIs a caregiver for a person with mild to moderate Alzheimer diseaseThe person with Alzheimer disease resides at their home or at the patient’s own home.

Exclusion criteria include the following:

The caregiver failed to meet the inclusion criteriaThe family member with Alzheimer disease has psychiatric disorders that were detected before the diagnosis of Alzheimer diseaseThe family members of the patient with Alzheimer disease have psychiatric disorders that were detected before the diagnosis of Alzheimer disease.

The type of intervention hypothesized for this study and the expected efficacy for the case group is comparable to the work of Küçükgüçlü et al [15]. The authors of this work, which included 30 individuals, obtained an average reduction in caregiver burden of 4.61 points, corresponding to an effect size of 0.243.

Assuming the same effect size in our group of cases, setting the statistical power at 90% and a significance level of .05, it was estimated through repeated-measures within-factors analysis of variance (ANOVA)—two groups and two measurement times (ie, baseline and follow-up)—that the total sample size expected must be at least 48 subjects. Considering a dropout rate of about 20%, the sample size increased to 58 subjects: 29 cases and 29 controls.

Recruitment was carried out during daily visits to the Alzheimer Centre of the IRRCS INRCA in Ancona, where the older person was accompanied by a family member. Once the criteria for participation were established and met, a proposal to join a support group was made, the caregiver chose whether or not to participate, and the caregiver was randomly placed in one of the two groups.

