### Data Analysis

A descriptive analysis of the sample will be carried out through univariate and bivariate statistical analysis. Continuous variables will reported as mean and SD or median and IQR, based on their distribution, and will be evaluated using the Shapiro-Wilk test. The comparison of variables between groups at baseline will be carried out by means of unpaired Student *t* tests or Mann-Whitney *U* tests, based on their distribution. Categorical variables will be expressed as absolute frequencies and percentages, and statistical significance will be evaluated using chi-square tests or Fisher exact tests, in the case of comparisons between small subsamples.

In the second phase, the analysis of follow-up data will be carried out in order to assess the effectiveness of the intervention. This phase of analysis involves the use of multivariate statistical techniques, in particular, repeated-measures ANOVA, in order to compare changes in outcome measures over time between the intervention group and the control group. In the case of different exposure times between subjects, the Cox regression model will be employed in order to identify factors associated with the change in key endpoints. Statistical significance will be set at *P*<.05.

Every effort will be made to collect all data within the specified time frame. In the case of missing and unrecoverable data on the primary endpoints, we will assume that these events are related to chance. Analyses will be performed by applying list-wise deletion to remove cases with missing values from the final database in order to obtain unbiased estimates.

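### The stated 90% power at 48 subjects is supported only for a change over time within a group, not for the between-arm difference in change that the trial tests

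*Protocol article*

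**What the plan says.** Under Participants, Recruitment, and Sample Size, the Protocol article relies on an earlier 30-person study that "obtained an average reduction in caregiver burden of 4.61 points, corresponding to an effect size of 0.243". It carries this over by "Assuming the same effect size in our group of cases", and "setting the statistical power at 90% and a significance level of .05". Of the method it says that "it was estimated through repeated-measures within-factors analysis of variance (ANOVA"), for "two groups and two measurement times (ie, baseline and follow-up"). The result is at least 48 subjects, raised to 58 (29 per arm) for a dropout of about 20%.

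Under Data Analysis, repeated-measures ANOVA is to be used "in order to compare changes in outcome measures over time between the intervention group and the control group". The Discussion gives the hypothesis that the experimental group will do better than the self-help group. Under Study Design and Intervention, controls also attend 16 facilitated sessions of 1.5 hours. The Introduction says of this kind of help: "Among the interventions for caregivers, support groups have been shown to be effective".

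**The concern.** The sizing paragraph describes a fall in burden, places it in the cases, and names a within-factors test. All three point to change over time inside a group. The analysis asks whether the two arms change by different amounts. The paragraph gives no figure for that difference: no expected change in controls, no contrast between arms, no SD and no correlation between the two measurements.

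An effect size that describes one arm's fall cannot be carried over unchanged to the contrast between two arms. If it is, the 90% attaches to a question the trial does not ask, and the power for the primary comparison may be far lower. Enrollment has closed and dropouts are not replaced, so the number is fixed. What can still be corrected is what readers are told the trial could detect.

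**Working it through.** **Inputs from the article:** mean reduction D = 4.61 points; effect size 0.243, metric not named; alpha 0.05; power 90%; k = 2 groups; m = 2 times; N = 48 before dropout and 58 after.

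**Assumed, because not stated:** correlation rho between the two measurements (0.5, with a range of 0.3 to 0.8), equal SD at both times, and equal arms.

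**1. Reproduce the 48.** For the within-factors F test, lambda = N·m·f²/(1 − rho), df1 = 1, df2 = N − 2. With f = 0.243 and rho = 0.5:

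- N = 48: lambda = 48 × 2 × 0.243² / 0.5 = 11.34, power 90.9%.
- N = 46: power 89.7%.

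The smallest equal-arm total is therefore 48, as stated. Other correlations do not give it: the need is 66 at rho = 0.3 and 30 at rho = 0.7.

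**2. The software option is not the fault.** With two groups and two times, the group-by-time test has the same lambda and degrees of freedom, so it also returns 48 at f = 0.243. What matters is which effect 0.243 describes.

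**3. Translate the case-group effect.** Within one arm that falls by D, the pre-post f is D/(2 SD). If that is 0.243, SD = 4.61/(2 × 0.243) = 9.49 points. For two equal arms, the group-by-time f is (difference in change)/(4 SD). With controls unchanged, the difference is D, so f = 4.61/(4 × 9.49) = 0.1215, half of 0.243.

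The time effect pooled over both arms is then D/(4 SD) as well, because the average change is D/2. A pooled time effect of 0.243 would need both arms to fall by D, and in that case the group-by-time effect is zero.

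**4. Power for the group-by-time test at f = 0.1215.** At N = 48 and rho = 0.5, lambda = 48 × 2 × 0.1215² / 0.5 = 2.83. With 20% dropout, 58 × 0.8 = 46.4 remain, so 46 is shown too.

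| rho | N = 46 | N = 48 |
|---|---|---|
| 0.3 | 28% | 29% |
| 0.5 | 36% | 38% |
| 0.7 | 55% | 57% |
| 0.8 | 72% | 74% |

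A simulation of change scores with 24 per arm at rho = 0.5 gave 38%. With all 58 analysed, power is 44%. If controls improve by half as much as cases, power at N = 48 and rho = 0.5 is 13%. For 90% power with controls unchanged, N is about 180 at rho = 0.5; at N = 48, rho would have to be about 0.87.

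**5. Secondary reading.** If 0.243 were 4.61/SD, the SD would be 18.97 and the group-by-time f 0.061. Power at N = 48 and rho = 0.5 is then about 13%.

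**6. What would make the 48 right.** A group-by-time f of 0.243 means a difference in change of 4 × 0.243 = 0.97 SD. At SD 9.49 that is 9.22 points, twice the 4.61 cited.

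**7. Detectable difference in change at 90% power** (4 times the f that gives 90%):

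| rho | N = 48 | N = 46 |
|---|---|---|
| 0.3 | 1.13 SD | 1.16 SD |
| 0.5 | 0.96 SD | 0.98 SD |
| 0.8 | 0.61 SD | 0.62 SD |

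**The case against.** The strongest reply is that the origin of 0.243 is inferred. The article does not call 4.61 points a single-group pre-post change and does not name the metric, and the cited study is not at hand. The calculation lists two groups, and the within and interaction tests need the same N at the same f. If 0.243 is already a group-by-time f, 48 is correct. This stands as a limit: it is not proven that the design lacks 90% power. But the wording about a reduction, about the cases and about a within-factors test points the other way, and nothing in the paragraph presents 0.243 as a contrast between arms.

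Three stronger readings are tempting and should not be drawn:

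- **That power is 13%.** This needs 0.243 to be 4.61/SD and also to have been entered as an f. The 48 reproduces with 0.243 as f, and there is no textual sign of that second slip. It is a lower case, not an equal one.
- **That the plan assumes an inert control.** The paragraph states no control assumption of any kind. Zero change is used above only as a simple reference case that favours the plan over an improving control.
- **That a null result will be taken as proof of no effect.** The article does not say how a null result will be read.

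It might also be said that such detail belongs in an analysis plan. The point, however, concerns what the article does state: a power, an effect, a test and an N that do not match its stated comparison.

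**Conclusion.** The point holds in this form: as written, 90% power at 48 subjects is supported for a within-group change over time and is not shown for the between-arm difference in change.

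On the plain reading (0.243 as the case-group pre-post f, controls unchanged), power for the primary comparison is about 36-38% at 46-48 evaluable and rho = 0.5, and about 28-74% over rho 0.3 to 0.8. Improvement in the active control arm lowers it further. The size rests on a metric, SD, correlation and control change that the article does not give, so it is a range. The direction holds at 48 evaluable for any correlation below about 0.87, whereas the stated 48 itself corresponds to 0.5.

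**What to change.** - Withdraw the 90% power claim for the between-arm comparison, unless 0.243 is shown to be a group-by-time f.
- State which metric 0.243 is, and the SD and correlation behind it.
- State what 58 randomised (about 46-48 evaluable) can deliver, as the between-arm difference in change detectable with 90% power: about 0.96-0.98 SD at rho = 0.5, running from 1.13-1.16 SD at rho = 0.3 to 0.61-0.62 SD at rho = 0.8.
- Report the primary between-arm effect with its confidence interval.

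The cost is a rewritten sample-size paragraph and a less favourable power statement. No participants are added, and the design and conduct do not change.

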### Randomization

This study has a single-blind design, as far as the evaluator is concerned, since the characteristics of the treatment do not allow for double- or triple-blind experimental procedures. A randomization technique based on a single sequence of random assignments was used. A list of random numbers generated by the computer was used, and subjects were assigned a number based on their order of inclusion in the study. According to the technique described above, the 58 subjects were randomly assigned to one of the two study groups. Randomized subjects leaving the study will not be replaced, as a dropout percentage has already been considered when estimating the sample size.

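### The allowance for about 20% dropout was added to the wrong base: 58 randomised keeps the required 48 only up to 17.2% dropout (minor)

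*Protocol article*

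**What the plan says.** Under Participants, Recruitment, and Sample Size, the protocol article takes from a cited study of 30 individuals a reduction in caregiver burden of 4.61 points, "corresponding to an effect size of 0.243". It plans for a repeated-measures within-factors ANOVA with "two groups and two measurement times (ie, baseline and follow-up"), "setting the statistical power at 90% and a significance level of .05", and concludes that "the total sample size expected must be at least 48 subjects". The dropout step follows: "Considering a dropout rate of about 20%, the sample size increased to 58 subjects: 29 cases and 29 controls".

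The Randomization section relies on that step: "Randomized subjects leaving the study will not be replaced, as a dropout percentage has already been considered when estimating the sample size". The Data Analysis section says that cases with missing values will be removed by list-wise deletion.

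**The concern.** The article prints both the inputs and the result of the dropout step, and they do not agree. If 48 is the floor and one in five of those randomised is lost, 58 is too few. It is the number obtained by adding 20% of 48 to 48, whereas the loss is 20% of everyone randomised.

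Two other parts of the plan depend on the figure. The decision not to replace dropouts is justified by the allowance already made for them. List-wise deletion means that a participant without a follow-up value contributes nothing to the analysis, so partial data do not soften the shortfall. At stake is whether the stated sample delivers the stated minimum, and with it the stated 90% power, at the dropout rate that the plan itself assumes.

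**Working it through.** **Inputs from the article.** Minimum 48 in total; dropout about 20%; 58 randomised, 29 per group; no replacement; list-wise deletion; significance level .05; power 90%; effect size 0.243; two groups and two measurement times.

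**Inputs assumed.** The article does not name the effect-size metric and gives no correlation between the two measurements. I read 0.243 as Cohen's f and take rho = 0.5, because together they reproduce the article's 48. Other values of rho are shown below.

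**1. Reproducing the 48.** For the within-factors test with m = 2 times and 2 groups, the noncentrality is lambda = N × m × f² / (1 − rho), with 1 and N − 2 degrees of freedom. At N = 48: lambda = 48 × 2 × 0.243² / 0.5 = 11.34.

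| N | Power (f = 0.243, rho = 0.5) |
|---|---|
| 46 | 89.7% |
| 47 | 90.3% |
| 48 | 90.9% |

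The smallest N that reaches 90% is 47, and equal groups make it 48. The article's figure is reproduced.

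**2. Reproducing the 58.** 48 × (1 + 0.20) = 57.6, rounded up to 58. This matches the stated figure.

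**3. The inflation that keeps 48.** 48 / (1 − 0.20) = 60, or 30 per group. Check: 60 × 0.80 = 48.

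**4. What 58 delivers.** At 20% dropout, 58 × 0.80 = 46.4, so about 46 evaluable (29 × 0.80 = 23.2 per group). The shortfall against 48 is 1.6, about 2 people.

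**5. The dropout that 58 tolerates.**
- To keep the stated 48: 1 − 48/58 = 10/58 = 17.2%.
- To keep 47, the smallest N with 90% power under the assumptions: 1 − 47/58 = 11/58 = 19.0%.

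**6. Sensitivity to the unstated correlation.** At N = 46, power is 83.7% with rho = 0.4, 89.7% with rho = 0.5 and 95.0% with rho = 0.6. The starting N also moves: the minimum for 90% power is 65 with rho = 0.3, 47 with rho = 0.5 and 29 with rho = 0.7. Steps 2 to 4, and the 17.2% in step 5, do not depend on rho or on the effect-size metric.

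**The case against.** The strongest reply is that almost nothing follows from the slip. The article says about 20%, not exactly 20%. Under the assumptions that reproduce 48, the 90% target is already met at 47, so 58 holds it up to 19.0% dropout, which can fairly be called about 20%. At exactly 20% the power falls 0.3 percentage points short of 90%. A gap of about 2 people lies well inside the uncertainty of any planned dropout rate. Enrolment ran until September 2022 and the Randomization section reports the 58 as already assigned, so a target of 60 can no longer be acted on.

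Most of this stands, and it sets the weight of the point. It does not remove the error. The article states its floor as 48, not 47, and against that floor the margin ends at 17.2%. The figure 58 equals 20% added to 48 and rounded up, and nothing elsewhere in the article corrects it or tells the reader where the margin ends.

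A reader might go further and infer that the trial is materially underpowered because of this step. The documents do not support that: the loss between 48 and 46 is 1.2 percentage points of power (90.9% to 89.7%). A reader might also take 89.7% as the plan's own figure. It is not, since both the metric and rho = 0.5 are inferred, and the choice of rho moves the result far more than the two missing people do.

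**Conclusion.** The point holds as a minor arithmetic error. Three statements conflict when the rate is taken at its face value of 20%: a minimum of 48, 20% dropout, and 58 randomised without replacement under list-wise deletion. The shortfall is 2 randomised (58 against 60), or about 2 evaluable (46 against 48), and this part rests only on the article's own numbers.

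The consequence for power is conditional on f = 0.243 and rho = 0.5. On those assumptions the design falls marginally under 90% at 20% dropout and meets it up to about 19%. The error alone gives no reason to doubt the trial's ability to answer its question, and no reason to call for more participants.

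**What to change.** In Participants, Recruitment, and Sample Size, restate the allowance along these lines: *58 randomised retains the required 48 only up to about 17% dropout; at 20% dropout about 46 would be evaluable, and power would be marginally under 90% on the assumptions that give 48.* State there the correlation between measurements that was used, and name the effect-size metric, so that the power remark can be checked.

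In Randomization, align the reason for not replacing dropouts with that wording, so that it claims cover for about 17% dropout and not for 20%.

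The cost is a few sentences and a slightly less favourable figure. Enrolment, allocation and analysis do not change.
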